## Abstract

**Background:**

Vascular cognitive impairment (VCI) persistently impairs cognition and the ability to perform activities of daily living, seriously compromising patients’ quality of life. Previous studies have reported that disorders of serum iron metabolism and iron deposition in the brain can lead to inflammation, abnormal protein aggregation and degeneration, and massive neuronal apoptosis in the central nervous system, which in turn leads to a progressive decline in cognitive processes. Our previous clinical studies have found acupuncture to be a safe and effective intervention for treating VCI, but the specific mechanisms require further exploration.

**Objective:**

The objective of the trial is to evaluate the clinical efficacy of Tongdu Xingshen acupuncture and to investigate whether it can improve VCI by regulating brain iron deposition and body iron metabolism.

**Methods:**

In total, 42 patients with VCI and 21 healthy individuals will participate in this clinical trial. The 42 patients with VCI will be randomized into acupuncture and control groups, while the 21 healthy individuals will be in the healthy control group. Both the control and acupuncture groups will receive conventional medical treatment and cognitive rehabilitation training. In addition, the acupuncture group will receive electroacupuncture treatment with Tongdu Xingshen for 30 minutes each time, 6 times a week for 4 weeks. Meanwhile, the healthy control group will not receive any intervention. All 3 groups will undergo baseline assessments of brain iron deposition, serum iron metabolism, and neuropsychological tests after enrollment. The acupuncture and control groups will be evaluated again at the end of 4 weeks of treatment, as described earlier. By comparing neuropsychological test scores between groups, we will examine the efficacy of Tongdu Xingshen acupuncture in treating VCI. Additionally, we will test the correlations between neuropsychological test scores, brain iron deposition, and body iron metabolism indexes to explore the possible mechanisms of Tongdu Xingshen acupuncture in treating VCI.

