**Figure 1 figure1:**
[figure not shown]
Flowchart of the trial. CDR: Clinical Dementia Rating; MMSE: Mini-Mental State Examination; MoCA: Montreal Cognitive Assessment; SWI: sensitivity-weighted imaging; VCI: vascular cognitive impairment.

**Table 1 table1:** Timing of treatment assessments and data collection.

Time point			Enrollment (week –1)		Baseline assessment (week 0)		Treatment phase (weeks 1-4)		Assessment of efficacy (week 5)
Sign informed consent			✓						
Demographic information			✓						
Medical history			✓						
Disease history			✓						
Randomization			✓						

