**Cognitive function assessments**									
	MMSE^a^			✓				✓	
	MoCA^b^			✓				✓	
	CDR^c^			✓				✓	

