**Blood detection**									
	Serum iron metabolism indicators			✓				✓	
	SWI^d^ scanning								
	Brain iron content			✓				✓	
Safety evaluation					✓		✓		
Adverse event					✓		✓		

^a^MMSE: Mini-Mental State Examination.

^b^MoCA: Montreal Cognitive Assessment.

^c^CDR: Clinical Dementia Rating.

^d^SWI: sensitivity-weighted imaging.

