### Inclusion and Exclusion Criteria

#### Inclusion Criteria

Inclusion criteria are as follows: (1) aged 18-75 years, male or female; (2) patient or informant reports of memory loss or other cognitive impairment lasting for at least 3 months and not using any medication to improve cognitive function prior to enrollment; (3) diagnostic criteria for VCI are met (Western medical diagnostic criteria refer to the *2019 Chinese Guidelines for the Diagnosis and Treatment of Vascular Cognitive Disorder* and Chinese medical diagnostic criteria refer to the *Diagnostic, Identification and Efficacy Determination Criteria for Vascular Dementia*); (4) imaging evidence (computed tomography or magnetic resonance imaging) to support cerebrovascular disease; (5) clear cognitive dysfunction, as assessed by the MMSE (no education: MMSE score≤17, primary school: MMSE score≤20, or junior school or above: MMSE score≤24) and MoCA (MoCA score < 26 points); and (6) consciousness and stable vital signs.

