### Randomization

To ensure balanced comparability between groups, we will use SPSS software (version 25.0; IBM Corp) to generate a random sequence, and 42 participants with VCI who meet the inclusion criteria will be randomly assigned to the acupuncture and control groups at a ratio of 1:1. In addition, the 42 numbered random sequences as well as the grouping scheme will be placed independently in sealed opaque envelopes, which will be opened only when a patient with VCI is enrolled. The randomization and concealment processes described earlier will be carried out by an independent third-party statistician who is not involved in any subsequent parts of this study.

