### Blinding

Because of the limitations of the protocol and the specific nature of acupuncture treatment, it will not be possible to blind the participants and the acupuncturists. However, to improve the quality and reliability of this study, the researchers will be blinded during the efficacy assessment, data collection and management, and statistical analysis of the results. Thus, the efficacy assessors, data collection and management personnel, and outcome analysis personnel will not be aware of the grouping of the trial and will not be allowed to communicate with each other or with the participants about the treatment. In addition, to prevent bias in the results by nonblinded participants or researchers, this study will only involve individuals who do not have a conflict of interest or preconceived position.

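### Table 1 puts randomization (week −1) before every baseline measure (week 0) in a trial with unblinded participants, and shows no MMSE or MoCA before randomization although eligibility depends on them

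*Protocol article*

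**What the plan says.** **Order of events.** In Table 1 the "Randomization" row is ticked in the same column as informed consent and history, the column whose heading begins "Enrollment (week –1". The rows under "Cognitive function assessments" (MMSE, MoCA, CDR), the row "Serum iron metabolism indicators" and the brain iron row each carry two ticks, best read as week 0 and week 5. The Randomization section says of the sealed envelopes: "which will be opened only when a patient with VCI is enrolled". The Abstract (Methods) says: "All 3 groups will undergo baseline assessments of brain iron deposition, serum iron metabolism, and neuropsychological tests after enrollment".

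**Blinding.** The Blinding section says "it will not be possible to blind the participants and the acupuncturists". The same section, the Outcome Measurements overview and the Neuropsychological Tests section keep the assessors unaware of the allocation.

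**Eligibility.** Inclusion criterion (5) requires "clear cognitive dysfunction, as assessed by the MMSE" with education-specific cut-offs, and a MoCA score below 26. The Randomization section assigns only patients who already satisfy the inclusion criteria. Participants and Recruitment Strategy mentions an initial screening without saying what it contains.

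**The concern.** A baseline measure is useful in a randomized comparison because allocation cannot have influenced it. If the arm is known first, that guarantee is lost for any measure that depends on the patient's effort or on what the patient and family report. MMSE and MoCA are performance tests, and the CDR section describes a rating built from conversation with the patient and family. A patient disappointed or encouraged by the allocation may perform or report differently before any treatment has started.

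The interval between allocation and baseline is also a period in which patients can leave because of the arm they drew. Such a patient would have been randomized but would have no baseline record.

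Separately, the schedule does not show how the cognitive eligibility criterion is established before the envelope is opened.

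**Working it through.** No figure in the protocol depends on this order, so the check is mainly a comparison of statements.

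**1. Does randomization precede baseline?**

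| Source | Randomization | Baseline measures |
|---|---|---|
| Table 1 | Consent column, week −1 | First tick best read as week 0 |
| Randomization section | Envelope opened at enrollment | Not mentioned |
| Abstract, Methods | Not mentioned; participants already described as groups | After enrollment |

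The columns of Table 1 are not cleanly aligned in the extracted text. The two ticks for each cognitive, blood and imaging row stand two columns apart. That spacing fits either week 0 with week 5, or week −1 with the treatment phase. The second option conflicts with the Neuropsychological Tests section, which places the second assessment after 4 weeks of treatment. Week 0 and week 5 is therefore the reading that fits, and randomization comes first.

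**2. Can patients know their arm at baseline?** The envelope is opened at enrollment and participants are not blinded. Nothing in the article withholds the arm until baseline is complete, and nothing says when patients are told. Knowledge at baseline is possible and likely under the stated order, but it is an inference.

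**3. Which measures are exposed?** MMSE and MoCA (effort) and CDR (patient and family report). Serum iron indicators and susceptibility values do not depend on effort.

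**4. Which analyses would a baseline shift reach?** Let s be the difference between arms in baseline MoCA caused by knowing the allocation, and b the slope of follow-up score on baseline. The bias in absolute size is:

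- comparison of 4-week scores alone: 0
- change from baseline: s
- baseline-adjusted comparison: b × s

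The protocol gives neither s nor b. As pure assumptions, take s = 0.5 to 1 point and b = 0.7. The planning difference in the Sample Size section is 26.13 − 22.66 = 3.47 points.

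- Change score: 0.5 to 1 point; 0.5/3.47 = 14% and 1/3.47 = 29%.
- Adjusted: 0.7 × 0.5 = 0.35 and 0.7 × 1 = 0.70; 0.35/3.47 = 10% and 0.70/3.47 = 20%.

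The direction is unknown, because it depends on which arm shifts and which way.

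**5. Losses.** With 21 patients per arm, each patient lost between allocation and baseline is 1/21 = 4.8% of that arm.

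**6. Eligibility.** The Inclusion Criteria and the Randomization section together require MMSE and MoCA results before assignment. Table 1 shows neither test at or before the randomization visit. Either a screening test is missing from the table or the tick for randomization is in the wrong place. The article does not say which.

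**7. How many patients could still benefit?** The Results section reports at most 30 participants enrolled by May 15, 2024, without separating patients from healthy controls. Even if all 30 were patients, 42 − 30 = 12 remained to be randomized at that date.

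**The case against.** Several points on the other side are sound.

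- **Eligibility.** A reader might infer that eligibility is tested after the arm is known. The documents do not support that: the Randomization section assigns only patients who already meet the criteria, and an initial screening is mentioned. What stands is a conflict between Table 1 and the text.
- **Removals.** A reader might infer that patients who fail the cut-offs at week 0 are removed under rejection criterion (1). That criterion covers people included by mistake without a VCI diagnosis. It does not describe routine removal on week 0 scores.
- **Knowledge of the arm.** No statement says when patients learn their allocation, so it cannot be asserted that they know it at baseline.
- **The Abstract sentence.** Taken alone, it places baseline after enrollment, not after randomization, and it also covers healthy controls, who are never randomized. The order rests on Table 1 and the envelope sentence together.
- **The table.** The reading that puts baseline measures at week 0 also puts an intervention tick there, although treatment belongs to weeks 1–4. Fine timing should not rest on Table 1 alone.
- **The analysis.** The Statistical Analysis section names no change-score or baseline-adjusted method, and the Sample Size section uses 4-week MoCA scores. A reader might infer a 10% to 20% bias in the efficacy result. That does not follow: a comparison of 4-week scores is not moved by a baseline shift.
- **Assessor blinding.** It protects scoring. It does not protect patient effort, informant report or the decision to leave.

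These points narrow the concern. They do not remove the stated order or the conflict over eligibility.

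**Conclusion.** The point holds in limited form. As written, allocation precedes all baseline measures in a trial whose patients are not blinded. Baseline MMSE, MoCA and CDR may therefore be taken with the arm known, and losses before baseline may differ by arm. Table 1 and the eligibility text also disagree on whether the cognitive cut-offs are established before randomization.

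A baseline shift would matter for the comparison of groups at baseline and for any before-after or baseline-adjusted analysis. It would not matter for 4-week scores compared alone. Differential loss would remain a problem under any of these analyses. The percentages in the working show scale under assumed inputs and are not estimates. The conclusion assumes the week 0 reading of Table 1 and that the envelope is opened when the Randomization section says. If practice already follows the safer order, only the wording needs correcting. This is an inexpensive improvement that should be made, not a defect that invalidates the design.

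**What to change.** 1. For patients still to be recruited, confirm eligibility and complete MMSE, MoCA and CDR before the envelope is opened, with blood and SWI at the same visit.
2. In Table 1, move the randomization tick to the end of week 0, and show where the MMSE and MoCA results used for eligibility are obtained.
3. In the Randomization section, replace the envelope condition with: *opened only after eligibility is confirmed and baseline assessment is complete*.
4. For patients already enrolled, record the randomization and baseline dates. Report how many were assessed after allocation, and any losses between the two dates, by arm. Do not rely on a sensitivity analysis that excludes patients assessed after allocation: under the stated order it could exclude everyone enrolled so far.

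The cost is a schedule amendment during recruitment. No extra visits are needed.

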#### Neuropsychological Tests

Cognitive function will be assessed at baseline and after 4 weeks of treatment by a professional evaluator using neuropsychological tests, and the evaluator will not be aware of the current grouping. The following are the neuropsychological test scales that will be used in this experiment.

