### Statistical Analysis

All data will be statistically analyzed by professional statisticians using SPSS software (version 25.0). If the data involved satisfy the characteristic properties of a normal distribution with uniform variance, we will use the mean and SD to describe them; conversely, if the data are not normally distributed, we will use the median and IQR to describe them. All statistical results will be considered statistically significant at *P*<.05.

Neuropsychological scale scores, iron metabolism–related indicators, and brain iron deposition are all measurement data. Normally distributed data with uniform variance among 3 groups will be analyzed using 1-way ANOVA, followed by multiple comparisons using the least significant difference test, whereas those with nonnormal distributions will be compared using the Kruskal-Wallis test followed by the Mann-Whitney *U* test with Bonferroni correction. Correlations between neuropsychological scale scores and serum iron metabolism indexes and brain iron deposition in patients with VCI will be assessed using Pearson correlation analysis.

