### Innovations and Limitations

This is the first clinical randomized experimental protocol of our team to use iron metabolism as an entry point to explore the potential mechanisms of acupuncture for VCI using modern medicine. This trial will be conducted using rigorous methods, for example, the patients with VCI will be randomly assigned to 2 groups; the data will undergo blind statistical analysis; and the interventionists, efficacy evaluators, and statisticians will be separated. However, due to the specificity of acupuncture, this experimental protocol could not be double blinded. Moreover, we could not avoid gender bias during the random allocation process. Therefore, to ensure the reliability of the data, we still need to further expand the sample size.

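### The named efficacy tests make no use of the baseline scores the trial collects, which costs precision at 21 patients per arm

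*Protocol article*

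**What the plan says.** All references are to the protocol article.

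- **Efficacy comparison (abstract, Methods).** "By comparing neuropsychological test scores between groups, we will examine the efficacy of Tongdu Xingshen acupuncture in treating VCI".
- **Named tests (Statistical Analysis).** The section treats scale scores, iron-metabolism markers and brain iron alike as measurement data. For these it states: "Normally distributed data with uniform variance among 3 groups will be analyzed using 1-way ANOVA, followed by multiple comparisons using the least significant difference test". Non-normal data will be "compared using the Kruskal-Wallis test followed by the Mann-Whitney *U* test with Bonferroni correction". No covariate, change score or repeated-measures model is named.
- **Data available.** The abstract states: "All 3 groups will undergo baseline assessments of brain iron deposition, serum iron metabolism, and neuropsychological tests after enrollment". Patients in the two treated groups are assessed again at the end of treatment. The Neuropsychological Tests section confirms: "Cognitive function will be assessed at baseline and after 4 weeks of treatment by a professional evaluator using neuropsychological tests". Table 1 adds demographic information at enrolment.
- **Sizing (Sample Size).** The calculation uses 4-week MoCA means of 26.13 (SD 5.33) and 22.66 (SD 5.38) from previous work. It arrives at 64 per arm, and the trial then takes about one-third of that total, 42 patients.
- **Imbalance (Innovations and Limitations).** The authors write that "we could not avoid gender bias during the random allocation process". The only remedy they offer is a larger sample.

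**The concern.** In a randomised comparison of a score measured before and after treatment, the baseline value of that score is usually the best single predictor of the final value. Putting it in the model removes the variance it explains and corrects the estimate for whatever baseline gap randomisation happened to leave. The tests named here do neither.

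This matters more than usual in this trial. The protocol calculates 64 per arm and then accepts 21 because of scanning cost and the cooperation that scanning demands. Precision that cannot come from numbers has to come from the analysis. The remedy offered for sex imbalance, a larger sample, is the one the Sample Size section has already ruled out. Adjustment uses data already being collected.

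**Working it through.** **Inputs from the Sample Size section:** difference 3.47; SD 5.38 (the larger of the two); two-sided alpha 0.05 (Z = 1.96); beta 0.1 (Z = 1.282); 20% loss. The Trial Design section gives 21 per group. After 20% loss, 21 × 0.8 = 16.8, taken as 17.

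**Input not in the article:** the correlation r between baseline and week-4 MoCA. I assume a range of 0.3 to 0.8.

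**1. The protocol's own figure.** N = 2 × [(1.96 + 1.282) × 5.38 / 3.47]² = 50.5, so 51 per arm. Then 51 / 0.8 = 63.75, so 64. The stated 64 per arm reproduces. One-third of 128 is 42.7, which matches the 42 patients.

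**2. Unadjusted power at the actual size.** The standard error of the difference is 5.38 × √(2/21) = 1.66, and 3.47 / 1.66 = 2.09. A two-sided t-test has power of about 53%. At 17 per arm the standard error is 5.38 × √(2/17) = 1.85 and power is about 45%. The normal approximation gives 55% and 47%.

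**3. Power with baseline adjustment.** ANCOVA replaces the SD by SD × √(1 − r²).

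| Assumed r | Variance removed (r²) | Residual SD | SE, 21 per arm | Power, 21 per arm | Power, 17 per arm |
|---|---|---|---|---|---|
| unadjusted | 0% | 5.38 | 1.66 | 53% | 45% |
| 0.3 | 9% | 5.13 | 1.58 | 57% | 48% |
| 0.5 | 25% | 4.66 | 1.44 | 65% | 56% |
| 0.6 | 36% | 4.30 | 1.33 | 72% | 63% |
| 0.7 | 49% | 3.84 | 1.19 | 81% | 72% |
| 0.8 | 64% | 3.23 | 1.00 | 92% | 86% |

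These use 2n − 2 degrees of freedom. Spending one more on the covariate lowers each figure by about 0.1 percentage point or less. At r = 0.7, 21 adjusted patients per arm are worth 21 / (1 − 0.49) = 41 unadjusted.

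**4. If the compared score were the change from baseline.** Its SD is 5.38 × √(2(1 − r)), taking the baseline SD as equal. At 21 per arm power is about 41% at r = 0.3, 53% at r = 0.5 and 75% at r = 0.7. Each is below the ANCOVA figure, and a change score beats the plain week-4 score only when r exceeds 0.5.

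**5. Chance imbalance.** Assume the baseline SD is also 5.38; the article gives no baseline SD. The baseline difference between arms then has a standard error of 1.66 points. The probability of a gap of 2 points or more in either direction is about 23% (2 / 1.66 = 1.20). With equal SDs, a baseline gap carries into the unadjusted estimate multiplied by r. A 1.66-point gap shifts it by 1.66 × 0.5 = 0.8 points at r = 0.5, and by 1.66 × 0.7 = 1.2 points at r = 0.7, against a planned effect of 3.47.

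**The case against.** **The text does not say that raw week-4 scores are compared.** It leaves open whether the score is the week-4 value or the change. The ANOVA is described for three groups, while the abstract has only the two treated groups re-evaluated, so the three-group test fits most naturally at baseline. The two-arm efficacy comparison is therefore under-described. This stands as a caution: that baseline is wholly unused is an inference from the tests named and from sizing on 4-week scores. It does not remove the point, because no named test carries a baseline term and a change score would still be less efficient than ANCOVA.

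**Covariates may be left to a separate statistical plan.** The Data Collection and Management section refers to one. A silent protocol could rely on that, but this one names its between-group tests. A plan that followed them would be unadjusted, and a plan that used ANCOVA would depart from the published text.

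**The gain may be small.** The article gives no r. Entry requires MoCA below 26 and MMSE under education-specific limits, and restricting the baseline range tends to lower r. At r = 0.3 power rises only from 53% to 57%. This stands, and it is why the range starts there.

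**Stronger readings that a reader might infer do not hold:**
- That the unadjusted comparison is biased. It is unbiased on average, and its standard error already allows for chance imbalance.
- That most of the week-4 variance is predictable from baseline. That needs r above about 0.71, and nothing in the article supports it.
- That a baseline gap passes in full into the estimate. It is multiplied by r.
- That randomisation is simple. The Randomization section gives a software-generated 1:1 sequence in 42 envelopes and does not state the type.

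**Conclusion.** The point holds as one of efficiency. The protocol names tests that cannot use the baseline value, and sizes the trial on 4-week scores, although that value is collected for each outcome in the randomised patients. The loss is precision and an uncorrected chance imbalance; validity is not at issue.

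Its size depends on an unknown correlation. At 21 per arm the gain runs from about 4 percentage points of power (r = 0.3) to about 39 (r = 0.8), and at 17 per arm from about 3 to about 41. These figures assume the protocol's difference and SD, equal SDs at both times, and a two-arm comparison. A reader might infer that adjustment makes up for the cut from 64 to 21 per arm. It does not, unless r is about 0.8: of the values tried, only that one passes the planned 90%, and only with no dropout.

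**What to change.** In the Statistical Analysis section, state the efficacy analysis as ANCOVA of week-4 MoCA on arm and baseline MoCA, in the acupuncture and control arms only, reporting the adjusted difference with its 95% confidence interval.

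Allow at most one or two further prespecified covariates. Sex would answer the concern raised in Innovations and Limitations; education is another candidate. A longer list is too much for 42 patients, or about 34 after the assumed loss, and the gain shown above comes from the baseline score alone.

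Use the same form, each with the outcome's own baseline, for MMSE, the serum markers and regional brain iron. For the five-level Clinical Dementia Rating use a rank-based or ordinal equivalent that takes account of its baseline level.

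The cost is wording in the protocol and analysis plan, fixed before the database is locked. No new data, visits or patients are needed.
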